#### Exclusion Criteria

The exclusion criteria are: (1) individuals who are currently receiving weekly structured psychotherapy; (2) individuals who meet the DSM-V criteria for severe alcohol/substance use disorder in the past 3 months, or who demonstrate clinically significant suicidal ideation defined as imminent intent, or who have attempted suicide in the past 6 months; and (3) individuals with comorbid diagnoses of borderline personality, bipolar disorder, schizophrenia, and/or obsessive compulsive disorder.

### Intervention

All subjects are provided standard psychiatric care, involving 1 monthly session that focuses on appropriate medication, with session durations from 15 to 30 min. Experimental subjects receive the additional intervention, consisting of a CBT-M software program (in collaboration with Nex J Health, Inc), which is accessed online. Interactions with the online workbooks is combined with navigation-coaching (total 24 hours duration), primarily delivered in phone and text message interactions. In addition, each participant is given a Fitbit-HR Charge 2 that assesses physical steps and 24-hour heart rate in 5-second (averaged) durations (the software permits daily monitoring). The intervention content builds on 2 prior successful Web-based CBT-mindfulness RCTs with students [9,10,13,15-17] and on effective methods with other populations demonstrated in previous RCTs [52-55]. The online workbook content includes 24 chapters reflecting multiple topics (eg, Living By Your Truths, Overcoming Wired-ness and Tired-ness, Mindfulness and Relationships, Loss and Grief, and Resilience, Befriending Ourselves, Befriending Your Body with Exercise, Body Image and Mindfulness, Intimacy, Forgiveness, Overcoming Procrastination, Dealing with Negative Moods, Stress Resilience, Overcoming Performance Anxiety, and Cultivating Inspiration) covered sequentially on a weekly basis with the navigator-coach. In summary, the key intervention features are 24-hour access and CBT-mindfulness contents that address specific symptoms and generic depressive experiences.

### Hypothesis

The CBT-M online intervention will be associated with statistically and clinically significant between-group differences (benefits) when treatment groups and control groups are compared, using both intention-to-treat (ITT) and per protocol analyses (PP). The ITT will proceed in a standard manner, whereas the PP will be based on the 24-week and 24-session structure of the intervention. All subjects who fail to attend 50% of the sessions (ie, <12 sessions) will be excluded from the PP.

### Outcome Measures

#### Primary Outcome

The primary outcome measure is the BDI-II [50].

#### Secondary Outcomes

The secondary outcomes assess anxiety (Beck Anxiety Inventory) [56], depression (ie, Quick Inventory of Depressive Symptomatology) [57], 24-item Hamilton Depression Rating Scale (HDRS-24; with a blinded interview-rater) [58], mindfulness (5-Facet Mindfulness Questionnaire) [59], and pain (Brief Pain Inventory) [60].

All self-report measures and the HDRS-24 interview are carried out at the same CAMH Mood and Anxiety research clinic in identical assessment rooms. The HDRS-24 interview-rater is blinded to intervention and control conditions for the trial duration.

## Results

### Analyses

Data obtained from participants during the study visits are de-identified and stored as electronic case reporting forms (CRFs) on the CAMH REDCap system and physical CRF paper copies in a locked cabinet. Participant characteristics are summarized via descriptive statistics. Group equivalence at baseline in terms of demographic and clinical variables is assessed.

### Primary and Secondary Outcomes

The monthly rate of recruitment is calculated and the level of retention will be presented in the proportion of enrolled participants completing study outcomes at each time point.

The effect of the intervention on the primary clinical and secondary outcomes will be assessed through separate analysis of covariance (ANCOVA) models that have changed from baseline to 6 months as the dependent variable, the baseline value of the outcome as a covariate and the group assignment as a categorical variable. The treatment effect, its effect size (Hedges’ g), and 95% CIs for the treatment effect and within-group changes from baseline to one year will be calculated from the ANCOVA model. The sensitivity of results to missing data will be evaluated by running a purely data-based multiple imputation procedure, as well as the imputation of missing values on a case-by-case basis using expert opinion and patient history.

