**Objective:**

We will conduct a randomized controlled trial to compare online mindfulness-oriented cognitive behavioral therapy (CBT-M) combined with standard psychiatric care versus psychiatric care alone in youth diagnosed with major depressive disorder. We will enroll 168 subjects in the age range of 18 to 30 years; 50% of subjects will be from First Nations (FN) backgrounds, whereas the other 50% will be from all other ethnic backgrounds. There will be equal stratification into 2 intervention groups (INT^1^ and INT^2^) and 2 wait-list control groups (CTL^1^ and CTL^2^) with 42 subjects per group, resulting in an equal number of INT^1^ and CTL^1^ of FN background and INT^2^ and CTL^2^ of non-FN background.

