### Recruitment and Randomization

Subjects are identified from the wait-lists for services at the Centre for Addiction and Mental Health (CAMH) and through contacts with multiple Toronto-based clinics. Eligible patients interact with a research coordinator who reviews and explains the study. Eligibility is ascertained in person followed by written consent before randomization. The identification of most subjects follows CAMH procedures where research coordinators identify potential participants by prescreening new clinic referrals and notifying the investigative team and the client’s clinician about potential study eligibility. The clinician then asks the client if she/he is willing to meet with a study team member to explore participation. Only when a client agrees, is she/he approached.

A biostatistician at the Department of Biostatistics at University Health Network ([name]) performed an electronic randomization of participants with study IDs to the different groups (INT^1^, INT^2^, CTL^1^, and CTL^2^). The information regarding each study ID with its respective group allocation was transferred onto cards and placed in individually sealed envelopes. After a participant had completed the baseline questionnaires, the research coordinator opened the next envelope in the series to determine participant group allocation and their respective study ID.

On the basis of a careful review of previously successful studies [38,39,41], we determined a sample size of 42 participants per group in 4 groups (total of n=168). Type I error was set at alpha=.05 and power at 80%. Our projected sample size of 168 participants is deemed more than adequate for the detection of small to medium effect size. With an anticipated drop-out rate of up to 20%, we will recruit 208 participants (54 per group).

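### The primary ANCOVA has no First Nations (FN) term and does not say whether group has two or four levels, although the trial is stratified by FN background

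*Protocol article*

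**What the plan says.** All references are to the protocol article.

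- **Stratification.** The Objective in the abstract says "There will be equal stratification into 2 intervention groups" and two wait-list control groups. There and in the Aim, INT1 and CTL1 are the FN groups and INT2 and CTL2 the non-FN groups.
- **Randomisation.** Recruitment and Randomization describes "electronic randomization of participants with study IDs to the different groups (INT^1^, INT^2^, CTL^1^, and CTL^2". After the baseline questionnaires, "the research coordinator opened the next envelope in the series to determine participant group allocation and their respective study ID".
- **Sample size.** The same section says "we determined a sample size of 42 participants per group in 4 groups (total of n=168", with "Type I error was set at alpha=.05 and power at 80" per cent. It gives no numeric effect size.
- **Intended comparison.** The Aim and the Hypothesis both set intervention (treatment) groups against control groups.
- **Model.** Primary and Secondary Outcomes uses change from baseline to 6 months as the dependent variable. The model terms are "the baseline value of the outcome as a covariate and the group assignment as a categorical variable". A single treatment effect, with Hedges' g and a 95% CI, is to be taken from it.

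**The concern.** FN background is a fixed characteristic. It can define strata, but it cannot be allocated. The randomisation text nevertheless uses the word group for four labels that carry it, and the analysis text uses the same word for the model's only categorical term. Two models fit that wording:

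- A two-level factor (intervention, control), which leaves out the factor on which the trial is stratified.
- A four-level factor, which absorbs FN differences but needs a named contrast to answer the treatment question. None is named.

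The two differ in standard error. Under the second, the overall test and the treatment contrast also differ in what a significant result means. A primary analysis should not leave that choice open.

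**Working it through.** **Inputs.** From the article: 42 per group, four groups, 168 in all, alpha 0.05, power 80%. Assumed: two-sided testing, residual SD of 1 for baseline-adjusted change within strata, equal cells, and an FN/non-FN difference e in adjusted change. The article gives no value for e, so a range is shown.

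**The plan's own figure.** The 168 cannot be reproduced without an effect size. Back-solving for the pooled comparison of 84 against 84:

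d = (1.960 + 0.842) × √(2/84) = 0.432 SD.

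**Reading A: two levels, no FN term.** With equal strata, FN background is orthogonal to treatment, so the estimate is not biased. The FN difference goes into the residual:

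- residual variance = 1 + e²/4
- the model's standard error is too large by k = √(1 + e²/4)
- the nominal critical value of 1.974 (165 df) therefore acts as 1.974 × k

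The noncentrality at d = 0.432 is 0.432 × √42 = 2.80.

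| Assumed e (SD) | k | Effective critical value | Type I error | Power at 0.432 SD |
|---|---|---|---|---|
| 0 | 1.000 | 1.974 | 0.050 | 0.795 |
| 0.3 | 1.011 | 1.997 | 0.048 | 0.789 |
| 0.5 | 1.031 | 2.035 | 0.043 | 0.777 |
| 0.8 | 1.077 | 2.127 | 0.035 | 0.749 |

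Simulation of the ANCOVA (20,000 runs per setting) gave type I errors of 0.049, 0.047, 0.041 and 0.037 for the same four values. A noncentral F calculation that deflates the noncentrality by 1 + e²/4 puts power at 0.5 SD at 0.770, so about 0.77 is a fair summary.

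**Reading B: four levels, overall 3-df test.** Noncentral F with 3 and 163 df, λ = 42 × (sum of squared deviations of the four means). With no treatment effect the means lie at ±e/2, so λ = 42e².

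| Assumed e (SD) | λ | Chance of significance with no treatment effect |
|---|---|---|
| 0 | 0 | 0.05 |
| 0.2 | 1.68 | 0.16 |
| 0.3 | 3.78 | 0.33 |
| 0.4 | 6.72 | 0.56 |
| 0.5 | 10.50 | 0.77 |

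With a treatment effect of 0.434 SD and no FN effect, λ = 42 × 0.434² = 7.91. Power of the 3-df test is 0.637, against 0.798 for the 1-df contrast.

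**Treatment (two levels) plus FN stratum.** Simulated type I error was 0.047 to 0.052 for e from 0 to 0.8 SD. Power at 0.432 SD is about 0.79 whatever the value of e. A 1-df intervention-against-control contrast within a four-level factor also removes the FN difference from the error.

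**The case against.** The strongest reply is that the overall 3-df test appears nowhere in the article. The model is introduced to assess the effect of the intervention, and it is to yield one treatment effect with Hedges' g and a CI, which an overall F test cannot supply. The Aim and the Hypothesis name the same contrast. This stands, so Reading B shows what the loose wording permits and is not a description of the plan.

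The reply continues that under Reading A the harm is small and the error conservative, and that covariate detail is often left to an analysis plan. The size is conceded. But the article does list the model's terms, and the stratification factor is not among them.

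Three stronger readings are tempting, and the article does not support them:

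- **FN participants drawing non-FN labels.** A reader might infer this from one series of four labels. In equal shares, half would not fit a given participant, and skipping envelopes would expose upcoming allocations. But the Objective and the Aim state stratification, and the envelope sentence is compatible with one series per stratum. Neither a mixed series nor broken concealment is shown.
- **Treatment confounded with ethnicity.** With balanced strata this is not so for a two-level factor or for a 1-df contrast.
- **Separate FN and non-FN tests, each at 0.05.** No such tests are planned, so no family-wise error arises from them.

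**Conclusion.** The point holds as a defect of specification with a modest numerical consequence on the likelier reading. The stated ANCOVA is either a two-level model without the stratification factor or a four-level model without a named contrast.

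On the two-level reading the estimate is sound, and the cost is a standard error up to about 3% too large at 0.5 SD and 8% at 0.8 SD, with the loss of power shown above. The large figures, 16% to 77% significance without any treatment effect and 64% power, apply only if the overall test of a four-level factor were used, which the article's stated comparison argues against. All of them depend on assumed FN differences and on balanced cells. If FN background made no difference to adjusted change, Reading A would lose nothing and the overall test would keep its 5% error rate, though it would still lose power.

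On allocation, the finding is limited to a mismatch between the stratified design and the description of randomising to four labels.

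**What to change.** 1. In Primary and Secondary Outcomes, define the primary ANCOVA as treatment (two levels: CBT-M plus standard care, standard care alone), FN stratum (two levels) and baseline BDI-II. Name the 1-df treatment effect as the single primary test.
2. Put the treatment × FN interaction in a secondary model.
3. In Recruitment and Randomization, state that treatment is allocated within each FN stratum from that stratum's own envelope series, if that is what was done, so that the section agrees with the Objective and the Aim. If it was not, describe the procedure actually used.

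The cost is wording and one residual degree of freedom (164 instead of 165). No additional participants are needed.

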## Discussion

If hypothesized results are obtained, this intervention may be an important option for depressed youth. As it can be accessed wherever internet-based services are available, geographic barriers to high-quality treatment could be minimized. Acknowledged study limitations include the lack of blinding regarding administration of self-report measures other than the blinding maintained for the HDRS-24 assessment.

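### The expert-opinion imputation planned as one of two missing-data sensitivity analyses is subjective, has no stated rule or blinding, and tests no defined departure from missing at random

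*Protocol article*

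**What the plan says.** The section Primary and Secondary Outcomes of the protocol article analyses each outcome by ANCOVA of the change to 6 months, with "the baseline value of the outcome as a covariate and the group assignment as a categorical variable". It then turns to missing data: "The sensitivity of results to missing data will be evaluated by running a purely data-based multiple imputation procedure", and, alongside that, "the imputation of missing values on a case-by-case basis using expert opinion and patient history". The expert step is therefore a second sensitivity analysis, not the main analysis.

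Three other places bear on it:

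- Primary Outcome: "The primary outcome measure is the BDI-II", a self-report scale.
- Discussion: "Acknowledged study limitations include the lack of blinding regarding administration of self-report measures other than the blinding maintained for the HDRS-24 assessment". The HDRS-24, which has the blinded rater, is a secondary outcome.
- Recruitment and Randomization: "With an anticipated drop-out rate of up to 20" percent, the target of 168 is raised to 208.

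The Intervention section gives the online workbooks and the navigation-coaching by phone and text to experimental subjects only.

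**The concern.** A sensitivity analysis should show how far the conclusion depends on an assumption that the data cannot check. The expert step does not do this, for three reasons.

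- **It has no fixed rule.** Deciding case by case is the opposite of a pre-set procedure. Two panels could enter different values from the same files, and nobody could repeat the result.
- **It can favour an arm.** The article does not say that the experts are blind to allocation. A history that mentions coaching contact would identify the arm, and the value being supplied belongs to a self-report scale with no assessor blinding behind it.
- **It does not vary missing at random in a controlled way.** Standard data-based multiple imputation rests on that assumption. Expert values may depart from it, but by an amount and in a direction that nobody has set. Neither of the two analyses named shows how large a departure would overturn the finding.

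What is at stake is the interpretation. Agreement between the expert-filled analysis and the main result could be reported as robustness when it shows little.

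**Working it through.** **1. How many values could be affected.** The article starts from 168 (42 in each of 4 groups) and allows up to 20% drop-out. Inflation: 168 / (1 − 0.20) = 210, against 208 stated; per group 42 / 0.80 = 52.5, so 53, against 54 stated. Both are close. (54 × 4 = 216, which does not match 208; that is a separate matter and changes little here.) At the ceiling, 0.20 × 208 = 41.6, so about 42 participants, or about 21 per pooled arm, could have an outcome supplied by opinion.

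**2. Precision, if one value per patient is analysed as observed.** This condition is an assumption. Write r for the model SE divided by the true SE. The actual error of a nominal two-sided 5% test is 2 × [1 − Φ(1.96 r)].

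- r = √0.80 = 0.894 (imputed values merely counted as full observations): error 0.080.
- r = 0.80 (imputed values also carry too little scatter): error 0.117.

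A simulation of the ANCOVA used no true effect, 104 per arm, 20% missing completely at random, baseline correlation 0.5 and unbiased single imputation:

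| Residual variance that the experts' information explains | r | Type I error |
|---|---|---|
| none | 0.79 to 0.82 | 0.10 to 0.12 |
| 50% | about 0.90 | about 0.08 |
| 75% | about 0.93 to 0.95 | about 0.06 to 0.07 |

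Complete-case ANCOVA stayed near 0.05 in the runs where it was also fitted. The 0.12 end therefore describes experts who know nothing beyond baseline and group. A 3-month assessment and a patient history would normally do better than that.

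**3. Bias, if the values are tilted.** Suppose the imputed values are more favourable in one arm than in the other by t SD (assumed), with a share m of values missing. The estimate then shifts by m × t. With m = 0.20:

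- t = 0.25: 0.05 SD
- t = 0.50: 0.10 SD
- t = 1.00: 0.20 SD

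At m = 0.10 each shift halves.

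**4. Scale.** The article gives no numerical design effect, only a small-to-medium one. Against the mean Hedges' g of 0.47 that its Introduction cites from a review, the three shifts are 0.05 / 0.47 = 11%, 0.10 / 0.47 = 21% and 0.20 / 0.47 = 43%. A difference detectable with 80% power at two-sided 0.05 (sidedness assumed) is (1.96 + 0.84) × √(2/84) = 0.43 SD if strata are pooled, and (1.96 + 0.84) × √(2/42) = 0.61 SD for 42 against 42. A shift of 0.10 SD is 23% of the first and 16% of the second. Both benchmarks are derived here; neither is stated in the article.

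**The case against.** The strongest reply is that the primary result is not at risk. The expert step is one of two sensitivity analyses and changes no primary estimate, interval or test. This stands. A reader might infer that the trial's own type I error rises to 8 to 12 percent; the article does not support that, because no claim is planned on the p-value of this analysis and the multiple imputation stands beside it.

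Second, a reader might infer that the experts will know the arm. The article does not say so. It does not say what they would see, nor that coaching records form part of the history. It does say that study-visit data are de-identified, which is not the same as being blind to arm. The Discussion's remark on blinding concerns the administration of self-report measures, not the imputation. What remains is a risk that no stated safeguard closes.

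Third, single-value imputation is suggested by the contrast with multiple imputation but is not stated. Elicited ranges would also fit the wording, so the error figures are conditional.

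Fourth, the analysis plan is not shown and may contain delta-adjusted or reference-based analyses. Their absence from a condensed article is no fault, and the point does not depend on it. Opinion informed by why a patient left could also depart from missing at random. The objection here is to a method that the article does state, whose departure is uncontrolled.

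Finally, blinding and fixed rules would answer much of the bias and reproducibility concern without deleting the step. That is fair for those two points, but it would still leave the departure undefined.

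**Conclusion.** The point holds as a badly chosen sensitivity analysis, not as a defect of the primary ANCOVA. Four things follow from the text itself: the method is subjective, it has no reproducible rule, no blinding of the experts is stated, and its departure from missing at random has no defined size or direction.

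The figures are illustrations for that one analysis at the highest drop-out that the article expects: type I error of about 0.06 to 0.12 if single values are treated as observed, and a shift of 0.05 to 0.20 SD for a tilt of 0.25 to 1.0 SD. Lower drop-out shrinks them. The correction is worth making before outcome data are seen, because the robustness statement is otherwise open to challenge whichever way it falls.

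**What to change.** Keep the planned multiple imputation and replace the expert step with a pre-specified departure built on it. Two suitable forms, either or both:

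- a delta tipping-point analysis, worsening the imputed BDI-II scores of the intervention arm in fixed steps until the conclusion changes, and reporting the step at which it does;
- reference-based imputation, in which intervention-arm drop-outs are imputed from the control-arm trajectory.

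If expert imputation is kept at all, have it done blind to arm and under written rules fixed in advance, and label it supplementary.

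The cost is a change of wording in the analysis plan and a little more programming. Recruitment, visits and care are unaffected. The downside is that the robustness result may look less favourable than an expert-filled analysis would.

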## Discussion

If hypothesized results are obtained, this intervention may be an important option for depressed youth. As it can be accessed wherever internet-based services are available, geographic barriers to high-quality treatment could be minimized. Acknowledged study limitations include the lack of blinding regarding administration of self-report measures other than the blinding maintained for the HDRS-24 assessment.

